### Confounding

Based on the literature and clinical experience, we identified a number of confounders affecting both the exposure and the outcomes of our study. The modelled outcomes will be adjusted for baseline data (sex, age, IMD quartiles, smoking status and comorbidities) and time-varying covariates (thyroid function, cumulative time on the medical treatment, time since diagnosis, levothyroxine replacement, pregnancy and diagnosis of cancer). Table 2 presents the details of how covariates are defined and handled. Figure 1 depicts the directed acyclic graphs representing the relationship between the covariates. We will explore the relationships between the potential confounders and both exposures and outcomes independently in order to establish their potential role in this particular dataset.

**Table 2 T2:** Definitions of study covariates

Variable	Definition
Aetiology of hyperthyroidism	Identified based on Read codes and categorised in (1) Graves’ disease, (2) toxic nodular goitre and (3) undefined. The undefined category will consist of unspecified diagnosis and missing aetiology data.
Age	Age at index date
Baseline fT4	The highest measurement between 3 months prior to diagnosis and the index date
BMI	Normal (or underweight) <25 kg/m^2^, overweight 25–30 kg/m^2^ and obese ≥30 kg/m^2^; additionally, BMI status will be deduced from the Read code
Cancer diagnosis	Switch-type binary variable assuming lifelong status of cancer comorbidity
Frequency of GP visits	Time-varying variable of number of GP visits in a unit of time
IMD	IMD will be stratified into quintiles.
Levothyroxine (LT4) replacement	Switch-type binary variable assuming lifelong LT4 administration following development of hypothyroidism in radioiodine and thyroidectomy treatment groups
Pregnancy	Time-varying binary variable recording pregnancy
Pretreatment ATD	Cumulative time on ATD between diagnosis and the index date
Sex	Binary variable
Smoking status	As recorded at the index date, last observation carried forward if not available at the index date
TSH	Serial TSH, log-transformed for the analysis
Time since diagnosis	Time-varying variable measuring cumulative time since diagnosis

ATD, antithyroid drug; BMI, body mass index; GP, general practitioner; IMD, Index of Multiple Deprivation; TSH, thyroid-stimulating hormone.

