#### Cardiometabolic risks and mortality

The descriptive analysis of primary and secondary outcomes will provide useful summaries about the sample and the outcome measures. Besides the unadjusted descriptive statistics, such as the incidence rate of each outcome, simple graphics analysis will be provided.

Causal inference in the analysis of cardiometabolic outcomes and mortality will be undertaken using inverse propensity weighting (IPW). This method was empirically shown to be superior to other propensity score-based approaches in analysis of multiple treatments with a binary outcome.^27^ The propensity-score matching, even though well valuated in two-arm treatment, in multiple treatments might introduce bias; the IPW is more efficient in such scenario. Additionally, IPW method is more flexible and requires weaker unconfoundedness assumption.^28^

Generalised propensity weights with treatment category as dependent variable will be calculated in the multinominal logistic model.^29^ The model will be developed using the following covariates: age at the index date, sex, baseline serum fT4, aetiology of hyperthyroidism, smoking status, IMD, cumulative time on ATD between diagnosis and the index date, time since diagnosis and BMI status.

Variables related to treatment, as an outcome, at p<0.10 will be selected for inclusion in the multiple propensity weights.^30^ To identify these variables, we will conduct several regression analyses with the treatment as a dependent and each potential confounder as an independent variable. Furthermore, it will be investigated whether adding interaction terms or higher-order terms for continuous variables will improve the balance of the model. The Hausman test will be used to check the independence of irrelevant alternatives assumption, which is the main assumption of multinomial regression analysis.^30^ If this assumption is not met, multinomial probit analysis will be used instead.

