The estimation of propensity weights will be conducted by the method proposed by McCaffrey *et al*.^31 32^ The appropriateness of IPW analysis will be assessed by checking the overlap (positivity assumption). According to the positivity assumption, each patient should have a non-zero probability of being indicated to each treatment category. Lack of overlap in the distribution of observed pretreatment characteristics between groups receiving different treatment indicates the positivity assumption is violated. This overlap will be checked visually. If poor overlap is identified, we will use Rubin’s trimming method,^33^ allowing discarding non-overlapping cases.

Further, pairwise balance in the distribution of all included variables between the three treatment groups will be tested with linear regression for continuous variables, logistic regression for binary and multinomial logistic regression for nominal variables. The analysis will be done without and with adjustments. The propensity weights will be considered balanced if there are no statistically significant (p<0.05) differences between the likelihood of receiving a different type of treatment. If imbalances remain after weighting, a doubly robust estimation approach will be applied^32^; that is, the imbalanced variables will be added to the model.

While IPW will adjust for confounding at baseline, other time-varying adjustments will be applied to correct for the events between the baseline and the outcome. The proposed covariates are treatment with levothyroxine for developed hypothyroidism, log TSH levels and informative observations of number of GP visits in a unit of time.

Incidence rate ratios of outcomes will be calculated with Poisson regression and modelled adjusting for time-varying covariates as listed further. Time-to-event analysis with adjustments will be modelled. The appropriate model will be applied, depending on the proportional hazard assumption’s results: if the assumption holds—Cox proportional hazard regression will be used; if it is violated, alternative techniques such as time-varying measures in extended Cox models will be applied.

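### The fallback labelled doubly robust adjusts only for variables that fail a balance test, so it does not have that property and should be redefined or renamed

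*Protocol article*

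**What the plan says.** All of the following is in the protocol article.

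- **Propensity covariates** (Cardiometabolic risks and mortality): "age at the index date, sex, baseline serum fT4, aetiology of hyperthyroidism, smoking status, IMD, cumulative time on ATD between diagnosis and the index date", followed by time since diagnosis and BMI status. A screen is applied: "Variables related to treatment, as an outcome, at p<0.10 will be selected for inclusion in the multiple propensity weights". Interactions and higher-order terms for continuous variables are to be explored, judged by whether they improve balance.
- **Balance check** (same section): "pairwise balance in the distribution of all included variables between the three treatment groups will be tested with linear regression for continuous variables", with logistic or multinomial regression for the other variable types. The criterion is "The propensity weights will be considered balanced if there are no statistically significant (p<0.05) differences".
- **Fallback** (same section): "If imbalances remain after weighting, a doubly robust estimation approach will be applied", explained as "that is, the imbalanced variables will be added to the model".
- **Division of labour** (same section): the weights deal with baseline confounding. The further adjustments listed for the outcome models are post-index: levothyroxine, log TSH and frequency of GP visits.
- **Confounding section**: the modelled outcomes are to be adjusted for "baseline data (sex, age, IMD quartiles, smoking status and comorbidities", plus time-varying covariates.

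**The concern.** The protocol names a property and then defines a procedure that does not deliver it. Double robustness gives two chances to be right: a correct propensity model or a correct outcome model. Under the stated rule the second chance is largely absent, because the outcome model's baseline content depends on which variables fail a test.

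At stake is how far results on MACE, the other cardiometabolic outcomes and death can be trusted if the propensity model is imperfect. Age drives these outcomes and probably treatment choice too. A reader who sees the label would credit the estimates with a protection they lack.

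**Working it through.** The article gives no sample size, event count or effect size for this analysis, so there is no planned figure to reproduce. The check is by logic, then by illustrative simulation.

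**Step 1: what the outcome model contains, reading the Cardiometabolic risks and mortality section alone.**

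- All balance tests pass: treatment and post-index covariates only, with no baseline confounder.
- Some tests fail: the same, plus the failing variables. Age, smoking or fT4 stay out whenever they pass.
- A variable removed by the p<0.10 screen is not in the weights. The balance check covers included variables, so it is neither tested nor added.

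In each case the outcome model is generally not a correct model of the outcome given the confounders. Validity then rests on the propensity model.

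**Step 2: what the test can see.** Linear regression of a continuous variable on treatment compares weighted means. If treatment choice is curved in age and the propensity is linear in age, mean age may be balanced while the rest of the age distribution is not. Where event rates rise non-linearly with age, that difference confounds.

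**Step 3: three-arm simulation (every parameter assumed).** n=5,000, with 120 to 150 replicates per setting. Covariates: x1 and x2 standard normal, x3 binary with probability 0.5. Log odds of treatment against the reference arm:

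- arm 1: −0.8 + 0.3·x2 + 0.3·x3 + q(x1²−1)
- arm 2: −1.2 + 0.4·x2 − 0.2·x3 − 0.5q(x1²−1)

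Events are Poisson with log mean −2 + 0.4·x1 + 0.3·x2 + 0.3·x3 + 0.25(x1²−1), the mean capped at 5. Treatment has no effect, so both true rate ratios are 1.00. Weights are 1/p from a multinomial logit with main effects. The rule tests each included variable pairwise at p<0.05 and adds only those that fail. Cells show the rate ratios for arms 1 and 2.

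| Setting | Runs flagged | Stated rule | All covariates, main effects | All covariates, correct form |
|---|---|---|---|---|
| A. q=0.15 | 0% | 1.22, 0.93 | 1.12, 0.96 | 1.00, 0.99 |
| B. q=0.30 | 0% | 1.44, 0.90 | 1.24, 0.94 | 1.02, 0.97 |
| C. B, outcome linear in x1 | 0% | 1.06, 1.00 | 1.01, 1.01 | same |
| D. B, plus 0.4·x1 and −0.3·x1 in treatment choice | 100% | 1.30, 0.95 | 1.30, 0.95 | 1.01, 0.99 |
| E. D, outcome linear in x1 | 100% | 1.00, 0.99 | 1.00, 0.99 | same |
| F. D with q=0, outcome linear in x1, x1 absent from propensity | 0% | 1.18, 0.89 | 1.01, 1.00 | same |
| G. B, x1² in propensity | 0% | 1.00, 0.97 | 1.00, 0.97 | 0.98, 0.99 |

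A, B and F show bias with no test failing. D shows that the fallback can switch on and still not correct. C and E show settings where the rule does little or no harm. G shows that a correct propensity model is enough.

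**Step 4: two-arm simulation closer to the study (assumed).** n=4,000, a smaller arm of about 8%, event rate rising 8% per year of age, true rate ratio 1.00, treatment choice curved in age, propensity linear in age and smoking, 300 data sets for each of two curvatures.

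- Stated rule: a variable flagged in 2% and 18% of runs; mean rate ratios 0.85 and 0.82, that is 1−0.85=15% and 1−0.82=18% too low.
- Age and smoking always in the outcome model: 0.99 and 1.00. The SD was 0.18 against 0.19 under the rule in the first case, and 0.19 for both in the second.

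Repeats with other assumed curvatures gave 0.86 down to 0.72 for a propensity linear in age, so the size follows the curvature chosen. In the repeats that added age squared to the propensity, the estimate moved from 0.86, 0.80 and 0.76 to 0.98, 1.00 and 1.01 in one set, and from 0.81 and 0.72 to 0.97 and 0.93 in another.

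**The case against.** The strongest reply is that the two-arm simulation leaves out a step aimed at its scenario. The protocol will investigate higher-order terms and interactions, and does not make this conditional on a failed test. Adding age squared removed most of the bias, and it reduced the weighted mean-age difference in 83% to 93% of runs, so a search for better balance would usually favour it. The article also refers weight estimation to a cited published method, which the simulations replace with a plain logit. This stands: the 15% to 18% figures describe a reduced version of the plan. It does not remove the point, because the added terms are themselves judged by balance. If an improvement means turning a failed test into a pass, the search may not adopt the needed term.

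Second, the Confounding section says outcomes are adjusted for baseline age and smoking, among others. On that reading age would not be left out. But the later section gives baseline confounding to the weights, the Confounding list lacks fT4, aetiology and BMI, and adding only imbalanced variables would be partly redundant if that list always entered. The text is ambiguous and needs reconciling.

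Third, the remedy can be oversold. In the two-arm runs the comparator was the true outcome model. Settings A and B keep 1.12 and 1.24 when both models miss the curve. This stands, and is why flexible terms are needed.

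Two stronger readings are tempting and unsupported. A reader might infer that different treatment contrasts would carry different adjustment sets, because balance is tested pairwise. The article adds the variables to one model and does not say so. A reader might also infer that the protocol relies on this step as its safeguard against propensity misspecification, or calls the whole analysis doubly robust. It does neither: the label covers one conditional step triggered by residual imbalance, and overlap inspection, trimming and the Hausman check with its probit alternative are separate.

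**Conclusion.** The point holds in limited form. The step is covariate adjustment for residual imbalance and lacks double robustness, because the outcome model it defines omits confounders that pass the test. If the propensity model remains misspecified after the search for higher-order terms, bias can remain without any test failing.

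The conclusion about the label follows from the wording and needs no assumption. The size does. Biases of about 15% to 20% show the mechanism when the propensity is left linear in age. They depend on the assumed curvature, outcome model and arm size, omit the planned search and are not estimates for this study. With an adequate propensity model, or an outcome linear in the covariate, the rule did little harm (at most 6% in settings C, E and G). It would be wrong to infer that the results will be biased by this amount, or that every misspecification would go unnoticed.

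**What to change.** 1. Enter all prespecified baseline propensity covariates in the weighted outcome model for every outcome, whatever the balance result, with flexible terms for age and the other continuous variables. Report the standardised (marginal) contrast. Remove the rule that adds only imbalanced variables.
2. Reconcile the Confounding section with the Cardiometabolic risks and mortality section. State whether baseline variables enter the outcome model, the weights or both, and give one list. Comorbidities are named as confounders but are absent from the propensity list, while fT4, aetiology and BMI are in the propensity list but not in the Confounding list.
3. If the first change is not made, drop the term doubly robust and call the step covariate adjustment for residual imbalance.

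The cost is wording and a few model terms. The hazard ratio or rate ratio becomes conditional on the covariates unless it is standardised, which adds a computation. In the two-arm simulation precision was about unchanged.

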## Introduction

Hyperthyroidism is a common condition affecting 3% of women and 0.3% of men in the UK.^1^ Common clinical features indicating hyperthyroidism include weight loss, heat intolerance, tremor, palpitations and anxiety.^2^ Treatment is critical to minimise complications including atrial fibrillation and stroke that contribute to the observed 20% increase in mortality.^3^

There are three treatment options: antithyroid drugs (ATDs), radioactive iodine (I-131, radioiodine) or surgical, either as a total or hemithyroidectomy. ATDs are associated with a high rate of relapse (30%–70%),^4^ while treatment with radioiodine or thyroidectomy leads to the development of hypothyroidism, requiring lifelong levothyroxine replacement, which is seen in 80% of patients administered radioiodine and up to 100% undergoing thyroidectomy. Guidance recommends discussion of all three options with the patient.^5 6^ There is insufficient evidence to recommend one treatment over the others, although some studies indicate differences in cardiac events and mortality between the treatment modalities.^7 8^

Weight gain following various treatments for hyperthyroidism has been described.^9 10^ Clinicians commonly assume that the observed weight gain is a simple regain of weight lost prior to the initiation of treatment. However, an analysis of 1373 patients with hyperthyroidism has demonstrated a higher prevalence of obesity at 3 years of follow-up when compared with the age-matched and sex-matched background population (37% vs 26% in men, p<0.001; 32% vs 26% in women, p<0.001).^11^ These findings suggest excess weight gain beyond patients’ premorbid weight (weight overshoot). Additionally, the study showed significant differences in final weight gain compared with baseline between those treated with ATDs (5.4 kg, 95% CI 4.8 to 6.0) and those who received radioiodine but did not develop hypothyroidism (5.1 kg, 95% CI 4.3 to 6.1) when compared with those treated with radioiodine who developed subsequent hypothyroidism (7.1 kg, 95% CI 6.6 to 7.7). The extent of weight change in patients treated with thyroidectomy was not evaluated.

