#### Secondary objectives

Further, the effect of treatment and weight status on the incidence of major adverse cardiovascular events (MACEs), other cardiometabolic outcomes and mortality following each treatment modality will be evaluated.

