### Index date and follow-up

The index date in the cohort is the date of initiation of treatment for hyperthyroidism, which defines the treatment group (either ATD, radioiodine or thyroidectomy). There is a requirement of at least 12 months’ data available prior to the index date.

The natural history of weight changes will be modelled preindex and postindex date. While the follow-up for the analysis of outcomes will start at the index date, a minimum of 12-month follow-up is required for the inclusion.

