Proposed time-varying adjustments for both analyses will include postindex date data, that is, treatment with levothyroxine for developed hypothyroidism, logTSH levels and informative observations of number of GP visits in a unit of time. To allow for the fact that patients may die, a competing risks approach will be adopted for estimating comparative incidences for non-fatal events to allow for the impact of mortality as a competing risk.^22^

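### The cardiometabolic and mortality models adjust for post-index levothyroxine and TSH, so they do not estimate the total effect of treatment type, and no model without them is specified

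*Protocol article*

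**What the plan says.** The secondary objective concerns "the effect of treatment and weight status on the incidence of major adverse cardiovascular events (MACEs), other cardiometabolic outcomes and mortality" after each treatment modality. The section on cardiometabolic risks and mortality states: "Causal inference in the analysis of cardiometabolic outcomes and mortality will be undertaken using inverse propensity weighting (IPW"), with propensity weights built from baseline variables. Time zero is set under Index date and follow-up: "The index date in the cohort is the date of initiation of treatment for hyperthyroidism, which defines the treatment group".

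The cardiometabolic section then adds a second layer of adjustment for what happens after baseline: "The proposed covariates are treatment with levothyroxine for developed hypothyroidism, log TSH levels and informative observations of number of GP visits". It confirms the timing and the reach to both the incidence-rate and the time-to-event models: "Proposed time-varying adjustments for both analyses will include postindex date data".

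The Confounding section says in general terms that modelled outcomes will be adjusted for baseline data and for "time-varying covariates (thyroid function, cumulative time on the medical treatment, time since diagnosis, levothyroxine replacement, pregnancy and diagnosis of cancer"). Table 2 defines levothyroxine as a switch-type variable, "assuming lifelong LT4 administration following development of hypothyroidism in radioiodine and thyroidectomy treatment groups". The Introduction says of hypothyroidism needing lifelong replacement, "which is seen in 80% of patients administered radioiodine and up to 100% undergoing thyroidectomy". The Exposure section takes ATD as not causing permanent hypothyroidism, and treats long-term levothyroxine after ATD alone as a sign of unrecorded radioiodine.

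**The concern.** A covariate measured after the index date cannot influence a treatment group that is fixed on that date, so it cannot confound the baseline choice. If treatment changes the covariate and the covariate is related to outcome, conditioning on it removes the part of the treatment effect that runs through it. It can also introduce bias through unmeasured causes shared by the covariate and the outcome.

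Patients and clinicians want to know what follows from choosing one treatment over another, including any hypothyroidism that the treatment brings. If hypothyroidism or its replacement raises risk, the adjusted hazard and rate ratios would omit that contribution while being presented as the causal effect of treatment. The same would happen to weight if the general covariate list is applied there.

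**Working it through.** The documents give no effect size, event count or power figure for this comparison, so there is no stated number to reproduce. The check has three parts.

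**1. Place of the covariates, from the protocol's own statements**

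- *Treatment to levothyroxine/TSH.* The Introduction gives 80% after radioiodine and up to 100% after thyroidectomy. Under ATD, long-term levothyroxine is zero by construction: Table 2 switches the variable on only in the two definitive-treatment groups, and the Exposure section moves ATD patients on long-term levothyroxine to radioiodine. The sensitivity analysis for missed radioiodine excludes such patients, which also leaves none under ATD.
- *Levothyroxine/TSH to outcome.* The Introduction reports higher mortality at TSH below 0.1 and above 4.0 mIU/L, and more ischaemic heart disease and heart failure above 10.0 mIU/L. For weight, it reports a gain of 7.1 kg in radioiodine patients who became hypothyroid, against 5.1 kg in those who did not.
- *Timing.* The adjustment set is explicitly post-index.

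Levothyroxine and TSH therefore behave as consequences of treatment that are linked to outcome.

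**2. Size, illustrated with the Introduction's weight figures**

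Inputs: ATD 5.4 kg (95% CI 4.8 to 6.0); radioiodine without hypothyroidism 5.1 kg (4.3 to 6.1); radioiodine with hypothyroidism 7.1 kg (6.6 to 7.7); hypothyroid share p = 0.8, assumed to apply to this cohort.

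- Total difference, radioiodine minus ATD: 0.8 × 7.1 + 0.2 × 5.1 − 5.4 = 5.68 + 1.02 − 5.4 = **+1.3 kg**.
- Difference among patients without hypothyroidism: 5.1 − 5.4 = **−0.3 kg**.
- Standard errors from interval width / 3.92: 0.31 (ATD), 0.46 (no hypothyroidism), 0.28 (hypothyroidism). Treating the groups as independent:
  - second contrast: SE = √(0.31² + 0.46²) ≈ 0.55, 95% CI about −1.4 to +0.8 kg;
  - total: SE = √(0.8² × 0.28² + 0.2² × 0.46² + 0.31²) ≈ 0.39, 95% CI about 0.5 to 2.1 kg.
- For a general share p: 7.1p + 5.1(1 − p) − 5.4 = 2p − 0.3, which is positive for any p above 0.15. The direction of the total difference does not hinge on 80%.

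**3. Illustration for event rates, all effect sizes assumed**

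Simulated Poisson data: 200,000 patients per arm, 10 years, base rate 0.01 per year, no direct treatment effect. The probability of levothyroxine was 0 / 0.8 / 1.0 for ATD / radioiodine / thyroidectomy and fixed over time. The rate ratio h of the hypothyroid/levothyroxine state was 1.2 or 1.5. Analytic totals are 1 + 0.8(h − 1) for radioiodine and h for thyroidectomy: 1.16 and 1.20, or 1.40 and 1.50.

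| Scenario | Rate ratios vs ATD (radioiodine / thyroidectomy), levothyroxine not in model | Levothyroxine in model |
|---|---|---|
| h = 1.2 | 1.16 / 1.19 | 1.01 / 1.01 |
| h = 1.5 | 1.43 / 1.52 | 1.03 / 1.02 |
| No effect at all, plus an unmeasured cause of levothyroxine and outcome | 1.00 / 1.01 | 0.83 / 0.80 |

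In the last row, the unmeasured cause doubles the outcome rate and moves the probability of levothyroxine from 0.7 to 0.9 in the radioiodine arm. Across all scenarios run, standard errors of the treatment terms rose about 1.8- to 2.4-fold. The sizes depend on these assumptions. If the levothyroxine state affects the outcome rate, losing the indirect part does not.

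**The case against.** Several points on the other side have force.

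- *The estimand is not named.* The objectives speak of the effect of treatment without the word total, and under further assumptions the adjusted models could target a direct effect. This stands as far as it goes. But the plan does not name a direct effect or state the no-unmeasured-confounding assumption it would need, and the aim of comparing modalities to guide choice points to the total effect.
- *The covariates are only proposed, the causal diagram is not shown, and the article condenses a fuller protocol.* This softens certainty about the final models. No alternative outcome model is stated. The remark in the cardiometabolic section about working without and with adjustments belongs to the balance checks, and the unadjusted outcome results it names are descriptive.
- *The weight model's own section lists no levothyroxine or TSH regressors.* Correct: the reach to weight rests only on the general sentence under Confounding.

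A reader might also infer more than the documents support:

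- *That adjustment reverses the direction of the weight difference.* The −0.3 kg is well within error of zero. The figures show attenuation to about nil.
- *That the surgery-versus-ATD contrast becomes unidentifiable.* Levothyroxine switches on over time, the 100% is an upper bound, and hemithyroidectomy is included. The simulation used the extreme case and found imprecision, not failure.
- *That GP visit rate is an established mediator or collider.* The protocol includes it as an informative observation process and does not say that treatment changes it. It is post-index and may respond to treatment and emerging illness, but that is inference.
- *That cumulative ATD time is a post-treatment variable to be removed.* Table 2 defines it up to the index date, and the propensity model uses it as a baseline covariate. Only its listing as time-varying under Confounding is inconsistent.

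**Conclusion.** The point holds for post-index levothyroxine and log TSH in the Poisson and time-to-event models. As written, these models do not estimate the total effect of treatment type on cardiometabolic outcomes and mortality, and no weighted outcome model without these covariates is specified. This rests on the protocol's own statements about hypothyroidism after each treatment and about TSH and outcome.

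The documents give no figure for the size of the distortion in cardiovascular events or death; the rate ratios above are illustrations under assumed effects. For weight, the Introduction's figures suggest that adjustment would remove most or all of a difference of about 1.3 kg. That assumes the 80% share applies to that cohort and that the general covariate list is carried into the weight model. For GP visit rate the concern is plausible but not established by the documents. The matter should be settled before analysis, because it decides what the main comparison means.

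**What to change.** 1. Specify the main treatment-effect models for cardiometabolic outcomes, mortality and weight with treatment plus baseline confounders only, through weights or baseline covariates. Keep pre-index cumulative ATD time as a baseline confounder. State that the target is the total effect of treatment type.
2. Report models that add post-index levothyroxine, log TSH and GP visit rate as a separately labelled secondary direct-effect or mediation analysis, with its assumptions stated. Methods for time-varying mediators and confounders are one option there.
3. State in the weight-model section which covariates enter, so that the general sentence under Confounding does not bring post-index variables into the primary analysis.
4. Reconcile the listing of cumulative time on medical treatment as time-varying under Confounding with Table 2's pre-index definition.

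The cost is protocol wording and one fewer block of covariates in the main models. Every planned adjusted model can be kept as a secondary result, and no new data are needed.

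### The covariate list for the Poisson rate ratios has no follow-up-time or attained-age term and omits the time since diagnosis that the Confounding section promises

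*Protocol article*

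**What the plan says.** Two places in the Protocol article govern the adjustment of the rate ratios.

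- **Cardiometabolic risks and mortality.** The rate-ratio sentence reads "Incidence rate ratios of outcomes will be calculated with Poisson regression and modelled adjusting for time-varying covariates as listed further". The list it points to opens with "Proposed time-varying adjustments for both analyses will include postindex date data" and names "treatment with levothyroxine for developed hypothyroidism, logTSH levels and informative observations of number of GP visits in a unit of time". The same three items appear a little earlier in that section as the adjustments for events after baseline. Time since diagnosis appears there only among the covariates of the propensity model.
- **Confounding.** The text says "The modelled outcomes will be adjusted for baseline data (sex, age, IMD quartiles, smoking status and comorbidities") and for "time-varying covariates (thyroid function, cumulative time on the medical treatment, time since diagnosis, levothyroxine replacement, pregnancy and diagnosis of cancer"). Table 2 defines age as "Age at index date" and time since diagnosis as "Time-varying variable measuring cumulative time since diagnosis".

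Under Index date and follow-up, outcome follow-up starts at the initiation of the treatment that defines the group. No length of follow-up is given, overall or by arm.

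**The concern.** A Poisson rate model without a time term treats the event rate as constant over follow-up, given its covariates. MACE, heart failure and death become more common as people age, and diagnoses span 1996 to 2015, so follow-up will vary widely between patients. An arm with longer follow-up contributes more person-time at older ages and so shows a higher crude rate, even with no treatment effect. Propensity weights built at the index date balance patients at that date. They do not balance the ages at which person-time later accrues.

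The Cox model conditions on follow-up time and does not share the problem. The proportional-hazards check governs the choice of Cox model and would not reveal a missing time term in the Poisson model. The two analyses could therefore disagree for a purely technical reason, and the article does not say which would prevail. The rate ratios are one of the analyses named in the abstract.

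**Working it through.** The plan states no event rate, event count or follow-up by arm, so there is no figure of its own to reproduce. The check has a textual part and an illustrative part.

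**1. The two lists of time-varying terms**

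| Term | Confounding section / Table 2 | List for Poisson and time-to-event models |
|---|---|---|
| Thyroid function (log TSH) | yes | yes |
| Levothyroxine | yes | yes |
| GP visits | Table 2 only | yes |
| Time since diagnosis | yes | no |
| Cumulative time on medical treatment | yes | no |
| Pregnancy, cancer | yes | no |
| Time since index, attained age | no | no |

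The only term in either list that advances steadily with follow-up is time since diagnosis, and the model-specific list lacks it.

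**2. Size of the distortion if no time term is fitted**

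Assume that the arms are identical at index, there is no treatment effect, the hazard is h0·exp(g·t), events are few, and every patient in an arm is followed for T years. The mean rate is then h0·(exp(gT) − 1)/(gT), and the spurious rate ratio is the quotient of this expression for the two arms.

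- g = 0.05: T = 12 gives (e^0.6 − 1)/0.6 = 1.370; T = 11 gives 1.333; T = 10 gives 1.297. Ratios: 1.370/1.333 = 1.028 and 1.370/1.297 = 1.056.
- g = 0.10: T = 12 gives (e^1.2 − 1)/1.2 = 1.933; T = 11 gives 1.822; T = 10 gives 1.718. Ratios: 1.933/1.822 = 1.061 and 1.933/1.718 = 1.125.

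**3. Varying follow-up within arms**

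Numerical integration with h0 = 0.01 per year and censoring uniform from 1 to 20 years in one arm, and from 1 year to a shorter maximum in the other:

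| Shorter arm's maximum | g = 0 | g = 0.05 | g = 0.10 |
|---|---|---|---|
| 20 years (equal) | 1.000 | 1.000 | 1.000 |
| 18 years (mean about 0.8 years less) | 1.000 | 1.035 | 1.076 |
| 16 years (mean about 1.6 years less) | 1.000 | 1.072 | 1.160 |

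The distortion needs both a rising rate and unequal follow-up. The fixed-T figures in step 2 are not an upper bound.

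**4. What time since diagnosis would do**

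A simulation used 200,000 patients, a true rate ratio of 1, g = 0.08 per year of attained age, maximum follow-up of 20 against 12 years (mean about 9.2 against 6.0), and person-time split by year with a log offset.

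- Arm and age at index only: 1.21 (95% CI 1.19 to 1.24).
- Adding time since diagnosis, same diagnosis-to-index gap in both arms: 1.00 (0.98 to 1.03).
- Adding time since diagnosis, shorter-followed arm indexed 1 year later after diagnosis: 1.08 (1.05 to 1.10).
- That same 1-year-gap case with time since index instead: 0.99 (0.97 to 1.01).

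The residue follows from the definitions. Attained age equals age at index plus time since index. Age at index plus time since diagnosis counts the diagnosis-to-index gap twice. A 1-year difference in that gap then gives about exp(0.08 × 1) = 1.083, in line with the simulated 1.08.

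None of these calculations includes the three listed covariates or the propensity weights, so they show mechanism and order of magnitude only.

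**The case against.** A reader might infer that the Poisson analysis has no time term at all. The documents do not support this. The Confounding section adjusts the modelled outcomes for age and for a time-varying time since diagnosis, and step 4 shows that this term removes most or all of the distortion. The shorter list is introduced as proposed adjustments that will include certain data, and it also drops pregnancy, cancer and time on medical treatment, so it may be an abbreviation. Against that, the wording "Proposed time-varying adjustments for both analyses will include postindex date data, that is, treatment with levothyroxine for developed hypothyroidism" reads as an enumeration, and the same three items are given twice. This part of the objection turns the point into a conflict between two lists, but does not remove it.

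A reader might also infer that the rate ratios will be biased against antithyroid drugs, because pretreated radioiodine and surgery patients are indexed later. That is plausible but not shown:

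- No follow-up by arm is given.
- The proxy rule moves drug-only patients on long-term levothyroxine to radioiodine, and these must have been observed long enough to become hypothyroid.
- Treatment mix may have changed over the 1996–2015 diagnosis window.
- Pre-index drug time and time since diagnosis are in the propensity model, which shrinks a gap-driven difference to the extent that they can be balanced.

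Offsets and band widths are details a condensed article may leave to a fuller plan, and their absence is not held against it here. The outcomes concerned are secondary, and the Cox and competing-risks analyses stand beside the Poisson models. These arguments limit the consequence, but they do not tell the analyst which list to use.

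**Conclusion.** The point holds as a conflict with a statistical consequence. The list attached to the Poisson models lacks any follow-up-time or attained-age term and omits the time since diagnosis promised for modelled outcomes. An analyst who follows it literally fits a rate that is constant over follow-up given levothyroxine, log TSH and GP visits. With rates that rise with age, this biases the rate ratio against the longer-followed arm, whichever that is.

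The size cannot be known from the documents. Under assumed growth of 5–10% a year and fixed follow-up, it is about 1.03–1.06 for a 1-year difference (12 against 11 years) and 1.06–1.13 for a 2-year difference (12 against 10 years). It is nil if follow-up is distributed equally or the rate is flat. Applying the Confounding section's list would remove most of the bias, but not necessarily all of it if arms differ in the diagnosis-to-index interval. The Cox analysis is not affected.

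**What to change.** 1. Reconcile the covariate list under Cardiometabolic risks and mortality with the Confounding section and Table 2, and say which time-varying terms enter the Poisson models.
2. State that person-time is split and that the Poisson model includes time since index and attained age (or age at index plus time since index), with a log person-time offset. Time since diagnosis should not be the only time axis.
3. Report the distribution of follow-up by arm, so that readers can judge how far the rate ratios depend on this term.

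The cost is a short text change and a few lines of data preparation. Person-time must already be split to carry the time-varying covariates, and no new data are needed.
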